## Abstract

**Background:**

In the majority of patients with osteoarthritis of the knee the disease originates in the medial compartment. There are two fundamentally different approaches to knee replacement for patients with unicompartmental disease: some surgeons feel that it is always best to replace both the knee compartments with a total knee replacement (TKR); whereas others feel it is best to replace just the damaged component of the knee using a partial or unicompartment replacement (UKR). Both interventions are established and well-documented procedures. Little evidence exists to prove the clinical and cost-effectiveness of either management option. This provides an explanation for the high variation in treatment of choice by individual surgeons for the same knee pathology.

The aim of the TOPKAT study will be to assess the clinical and cost effectiveness of TKRs compared to UKRs in patients with medial compartment osteoarthritis.

**Methods/Design:**

The design of the study is a single layer multicentre superiority type randomised controlled trial of unilateral knee replacement patients. Blinding will not be possible as the surgical scars for each procedure differ.

We aim to recruit 500 patients from approximately 28 secondary care orthopaedic units from across the UK including district general and teaching hospitals. Participants will be randomised to either UKR or TKR. Randomisation will occur using a web-based randomisation system. The study is pragmatic in terms of implant selection for the knee replacement operation. Participants will be followed up for 5 years. The primary outcome is the Oxford Knee Score, which will be collected via questionnaires at 2 months, 1 year and then annually to 5 years. Secondary outcomes will include cost-effectiveness, patient satisfaction and complications data.

**Trial registration:**

Current Controlled Trials ISRCTN03013488; ClinicalTrials.gov Identifier: NCT01352247

## Background

Osteoarthritis in the knee affects different people in different ways. In the majority of patients with osteoarthritis of the knee the disease originates in the medial compartment [1]. There are varying forms of treatment for this and each aim to relieve pain and discomfort, to reduce stiffness and to minimise further damage to the joint. Such approaches include physiotherapy, drug therapy and surgery [2-5]. One of the surgical options is to replace the diseased joint with a prosthesis (arthroplasty) and there are different approaches in common use. Some surgeons feel that it is always best to replace both the knee compartments with a total knee replacement (TKR). Others feel it is best to replace just the damaged component of the knee with a partial or unicompartmental knee replacement (UKR). There is disagreement among knee surgeons with the majority supporting TKR and the minority UKR. Fewer than 5% of knee replacements worldwide are unicompartmental, although it is thought that up to 30% of patients requiring knee replacements have only unicompartmental disease that would be suitable for a UKR [1,6,7]. This variation in decision-making for patients with medial compartmental arthritis has been well illustrated in a recent linked study [8]. The study showed a high variation in decision-making (TKR or UKR) between four different surgeons (up to 59%). Reassuringly, the consistency of treatment choice (test re-test repeatability) for each individual surgeon remained high. The conclusions were that surgeons, given identical information, do not concur on treatment for patients with the same pathology and that consensus treatment for medial osteoarthritis of the knee remains in question.

There are arguments for both approaches. Both interventions are established and well-documented procedures. Each intervention is considered standard care. There exists little evidence, however, to prove the clinical and cost-effectiveness of either management option and decisions on treatment tend to have a large personal opinion component of the surgeon. The TKR supporters believe that the operation is less complex than UKR and thus, in the short-term TKRs are less susceptible to early problems and failures. They also believe that in the longer term the joint disease will progress to the other, normal, compartments of the knee [9,10], thus a UKR will ultimately fail and require revision to TKR anyway [11,12]. In contrast, the UKR supporters believe the UKR gives faster recovery [7,13], fewer complications [14], superior function[15], is more cost-effective than TKR [16], and it is associated with long-term survival of the joint [6,17].

Current patient management for medial osteoarthritis is based on limited evidence. There have been several individual cohort studies, indirect comparisons and retrospective studies but these have addressed specific aspects and many involve only short-term assessments. Such studies include a comparison between TKR and UKR of the kinematics [18], proprioception [19], ability to kneel [15], ease of revision [20-22] and success or revision after various procedures [23-26], appropriateness for specific pathology [27], accuracy of implantation [28-30] and complications [31,32]. No large, well-powered, multicentre randomised controlled trial has been undertaken to directly compare UKR with TKR. The only other previous attempt at comparing these operations on a large scale was that from one of the comparisons in the Knee Arthroplasty Trial (KAT) [33,34]. However, this comparison failed due to slow patient recruitment. The primary reason for this was that a new minimally invasive technique was introduced for UKR between trial design and recruitment - surgeons chose to learn the new technique rather than recruit for the trial. Joint registry data has shown a trend towards TKR having better survival (as assessed by the rate of revision surgery) [11,12], but other studies are characterised by low level evidence, consensus and peer influence [35-38]. In order to test the validity of these results, further investigation is required. Using an appropriate patient population and long-term assessments, the clinical and cost-effectiveness of both treatment options can be examined.

### Objectives

The primary objective for TOPKAT will be to assess the clinical and cost-effectiveness of TKRs compared to UKRs in patients with medial compartment osteoarthritis of the knee.

Secondary objectives include investigation of complications, patient satisfaction, and the cost implications of the knee replacements for patients and employers as well as healthcare providers.

## Methods/Design

### Study design

The design of the study is a single layer multicentre superiority type randomised controlled trial of unilateral knee replacement patients. The randomised controlled trial design will help reduce and prevent potential bias influencing the evaluation.

Participants will be randomised to either UKR or TKR. The trial has a combined equipoise/expertise approach. It enables surgeons who are not in equipoise to deliver only one of the two operations while also allowing surgeons in equipoise to provide both operations. A surgeon who is in equipoise (‘equipoise surgeon’) and has sufficient experience to perform both TKR and UKR will deliver the allocated operation (UKR or TKR). The same surgeon will perform the operation for both arms of the study.

Not all surgeons are able to exhibit this equipoise. They may hold a preference for one treatment over the other often due to experience/expertise with one type of operation. Interestingly, a surgeon may also believe the patient may benefit from one particular operation even though they may not be able to perform it themselves.

Equipoise is difficult to investigate or establish. Self declaration has been used as the main approach but in order to sufficiently secure this state the following aspects are important:

•The equipoise considered must be patient- or individual-based equipoise rather than an overall or general category equipoise based on operation type. The surgeon must consider their position for each individual patient. Only if they believe that either operation will be suitable for an individual patient can the patient then be recruited.

•No surgeon will ever knowingly perform what they consider a substandard surgical procedure.

In order to complete the trial by seeking to maximise surgeon participation, an ‘expertise’-based delivery of the intervention will also occur. For this approach there must be a surgeon with expertise in TKR and a surgeon with expertise in UKR in the same centre who will act together as a ‘delivery unit’. Patients recruited to the study who are under the care of such a surgeon (‘expertise surgeon’) will be randomised to one of the two groups and treated by the appropriate surgeon. This ‘expertise’ approach allows for those UKR surgeons who work alongside TKR surgeons to team up and participate in the study. Subsequent surgery may be carried out by a surgeon different to that at the initial consultation. In such cases the patient is internally referred to the other surgeon’s operating list. A study flowchart is detailed in Figure 1. No restriction is made upon the number of delivery units within a centre. A surgeon can only be in one delivery unit, that is, they are either an ‘equipoise surgeon’ or an ‘expertise surgeon’.

**Figure 1 F1:**
[figure not shown]
Consort study flow chart.

To ensure participating surgeons have appropriate expertise, a simple audit of participating surgeons’ routine practice will be undertaken. UKR surgeons must have had appropriate training, been practising the technique for at least 1 year and have performed the operation at least 10 times in the past year. They must also be aware of their clinical results and these must be acceptable to the study team. Implants used by UKR surgeons in the study must have good clinical results and be a commonly used knee system which does not require patella dislocation. TKR surgeons must satisfy similar criteria. They must have had many years experience with TKR and will use a conventional approach with patella dislocation. ‘Equipoise surgeons’, who deliver both operations, are required to satisfy the criteria for both operations, that is, they will have appropriate training in both operations and have performed a minimum of 10 UKR and 10 TKR procedures.

### Primary outcome measure

The primary outcome measure for TOPKAT is the Oxford Knee Score (OKS). This is a patient-reported outcome questionnaire specifically designed and developed to assess function and pain after TKR surgery; it is a validated and effective measure of change over time [39]. Although patients will be contacted annually, the primary analysis will be at 5 years (and 10 years (subject to additional funding) post randomisation. An early analysis at 1 year is also planned.

### Secondary outcome measures

•American Knee Society Score [40] - measures range of motion and function of the knee

•UCLA Activity Score [41] - measurement of patient activity level in arthroplasty patients with mid/lower level activity

•High Activity Arthroplasty Score (HAAS) [42] - measurement of patient activity accounting for patients with potentially higher levels of activity

•Radiographic features including signs of potential failure, that is, loosening

•EuroQol EQ-5D [43] - evaluation generic measure of health-related quality of life to be used for the economic evaluation

•Lund Score [44] - measurement of patient satisfaction

•Complications

•Length of hospital stay

•Re-operation rate (minor revision, major revision and other related procedure)

•Composite outcome assessment - combination of re-operation frequency and poor outcome in terms of OKS. The anchor based minimally important change (MIC) of the OKS will be used to identify poor outcome (‘lack of success’) for functional outcome [45]

•Adjunct score to the OKS (for younger/active patients)

### Health economics

The health economic evaluation proposed will take the form of a cost-utility analysis. Health outcomes will be assessed at each trial follow-up point using the EuroQol EQ-5D questionnaire and each patient’s resulting utility profile will be used to calculate the number of quality-adjusted life years (QALYs) they experience over the duration of the trial.

To estimate the direct healthcare costs associated with both types of knee replacement, information will be collected for each patient in the trial on the resources consumed during initial surgery (including time in theatre, implants used and hospital inpatient stay), and on any subsequent related healthcare use (for example, relating to complications and/or surgical re-operation including revision). Data on costs patients may incur as a result of their knee condition, including rehabilitation, will be recorded. Information will also be collected from patients on return to paid employment.

### Study setting

Five hundred patients will be recruited from approximately 28 secondary care orthopaedic units from across the UK including district general and teaching hospitals over a period of 3 years.

### Study participants

Participants with osteoarthritis of the medial compartment of the knee will be included in the study. Patients must satisfy general requirements for a medial UKR which are listed below as the inclusion criteria to be recruited to TOPKAT. It should also be noted that if patients meet the inclusion criteria with both their knees, only one knee (designated the study knee) will be operated on according to the randomised allocation assigned as the patient enters into the study. Knee specific measures will be collected (primarily) for the study knee. TOPKAT will not recruit patients with simultaneous bilateral knee replacements. Subsequent knee replacement on the other, non study, knee will be recorded but the subsequent operation will not lead to a further random allocation.

### Inclusion criteria

•Medial compartment osteoarthritis with exposed bone on both femur and tibia

•Functionally intact anterior cruciate ligament (superficial damage or splitting is acceptable)

•Full thickness and good quality lateral cartilage present

•Correctable intra-articular varus deformity (suggestive of adequate medial collateral ligament function)

•Medically fit showing an ASA of 1 or 2

### Exclusion criteria

•Require revision knee replacement surgery

•Have rheumatoid arthritis or other inflammatory disorders

•Are unlikely to be able to perform required clinical assessment tasks

•Have symptomatic foot, hip or spinal pathology

•Previous knee surgery other than diagnostic arthroscopy and medial menisectomy

•Previously had septic arthritis

•Have significant damage to the patella-femoral joint especially on the lateral facet.

### Recruitment and consent

Potential patients will be identified and approached in outpatient and at pre-assessment clinics by the participating surgeon (or their late stage trainee). At this stage patients will be provided with an ‘Invitation letter’ and information sheet which will explain why they have been approached and will provide further details about the study. Patients will indicate if they are willing to be contacted again by the research team, using the TOPKAT Yes/No (‘opt in’) form. Those patients who indicate ‘Yes’ will be contacted by local study staff to arrange a screening visit to assess their eligibility for the study. If the patient is identified during an outpatient appointment the screening visit could coincide with their pre-assessment clinic appointment. The pre-assessment appointments are routinely scheduled for a short time before their scheduled operation date. If patients were identified at their pre-assessment clinic appointment, an extra visit will have to be coordinated for the screening to take place before the patient’s operation date. Contact with the patient must be made at least 48 hours following introduction to the study.

Potential patients may also be identified from local databases. These patients will be sent a letter and a TOPKAT YES/NO form to return documenting if they are willing to be contacted subsequently.

During the screening visit patients will be asked to sign a consent form. This allows their details to be entered into the TOPKAT web-based data collection system. Patient details and all preoperative assessments will be recorded and a study number will be allocated.

Patients will be given sufficient time to accept or decline involvement. They will be free to withdraw from the study at any time without affecting their routine perioperative care.

### Study assessments

Preoperative assessments will include a patient reported questionnaire examining pain and function (OKS), activity level and healthcare resource use. In addition, the American Knee Society Score (AKSS), a clinical assessment of range of motion and function of the knee, will be carried out. Routine preoperative X-rays will also be collected.

Operative details will be recorded and routine postoperative X-rays collected.

Patients will be required to attend a clinic appointment for the AKSS assessment at 2 months, 1 and 5 years post operation. The first two visits will coincide with routine hospital follow-up visits for these knee replacement procedures.

A postal questionnaire (containing the OKS, UCLA, HAAS, EQ-5D, Lund, healthcare and patient resource use) will also be sent out at years 1 to year 5 post randomisation. Additional clinical and postal questionnaire assessments are planned for years 7 and 10 subject to funding. The components of follow-up are shown in Table 1.

**Table 1 T1:** Components of follow-up time points

	**Pre**	**2 months**	**1 year**	**2 years**	**3 years**	**4 years**	**5 years**	**7 years**	**10 years**
OKS (self-report function)	*▲*	*○*	*○*	*○*	*○*	*○*	*○*	*○*	*○*
AKSS (clinical exam)	*▲*	*▲*	*▲*				*▲*		*▲*
UCLA (self-report activity)	*▲*	*○*	*○*	*○*	*○*	*○*	*○*	*○*	*○*
High Activity Arthroplasty Score	*▲*	*○*	*○*	*○*	*○*	*○*	*○*	*○*	*○*
X-rays	*▲*	*▲**					*▲*		*▲*
EQ-5D	*▲*	*○*	*○*	*○*	*○*	*○*	*○*	*○*	*○*
Lund (patient satisfaction)		*○*	*○*	*○*	*○*	*○*	*○*	*○*	*○*
Complications		*▲*	*▲*	*○*	*○*	*○*	*▲*	*○*	*▲*
Healthcare and patient resource use	*▲*	*○*	*○*	*○*	*○*	*○*	*○*	*○*	*○*

*▲* = Collected at clinic visit *○* = Postal Questionnaires * = Immediately Post Op.

Due to the variation in waiting times for surgery at participating sites, it is possible that a small number of participants may receive their 1 year follow-up questionnaire (which is sent post randomisation) at a time point much earlier than 1 year post surgery when the clinical assessment is carried out. These patients will have their 1 year assessment too early in their recovery for the results to be valid and there will be great variation in follow-up time. In cases where there is more than 12 weeks between randomisation of a patient to treatment and their operation date, an additional OKS will be administered at the clinical assessment 1 year post surgery.

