#### Primary outcome - OKS score

Table 2 shows the number of subjects required in each randomised group to give either 80% or 90% power to detect differences in the OKS of 2.0, 3.0 and 4.0, at either the two-sided 1% or 5% significance level and with SD of 8.0, 9.0 or 10.0.

**Table 2 T2:** Sample size scenarios

**Number in each group**		**Mean difference in OKS**					
		**2.0**		**3.0**		**4.0**	
**Power**	**SD**	**1% sig level**	**5% sig level**	**1% sig level**	**5% sig level**	**1% sig level**	**5% sig level**
90	8.0	480	340	215	150	120	85
	9.0	600	430	270	190	150	110
	10.0	740	520	330	235	190	130
80	8.0	375	250	170	110	100	60
	9.0	470	320	210	140	120	80
	10.0	590	390	260	175	150	100

The minimal clinically significant difference of the OKS is judged to be 2.0, and the likely SD of the OKS is 8.0 [46]. A sample size of 500 patients (250 in each group) would provide 80% power to detect a difference of 2.0 at 5% (two-sided) significance level. Since it is possible that the SD of the OKS could be >8.0 [13], this size of sample would allow for the detection of a difference of 3.0 in OKS with a SD of 10.0 at 5% (two-sided) significance level and 90% power and also a difference of 3.0 at 1% (two-sided) significance level with 80% power.

Indeed, almost all of the above scenarios are detectable if the difference in OKS is 3.0 rather than 2.0. This difference of 3.0 in the OKS is equivalent to a typical category change in the American Knee Society Score [40]. Furthermore, a difference in the OKS of 4.0 would, with 250 patients per group allow for some subgroup analyses. As previous research (the Bristol RCT) suggests that the difference between the groups is indeed likely to be >2.0 [6], a sample size of 250 in each arm would allow for some non-response yet still detect differences. As the statistical analysis will adjust for the baseline value and account for the surgical delivery unit this will likely increase precision. Offsetting this will be any missing data which would have the reverse impact.

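### The 5-year primary OKS is scheduled by post only; the 5-year trial clinic could serve as an inexpensive back-up for forms still outstanding

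*Protocol article*

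**What the plan says.** Under Primary outcome measure, the OKS is the primary outcome and "the primary analysis will be at 5 years (and 10 years (subject to additional funding) post randomisation".

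Under Study assessments, two 5-year contacts run on different clocks:

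- The questionnaire is counted from randomisation: "A postal questionnaire (containing the OKS, UCLA, HAAS, EQ-5D, Lund, healthcare and patient resource use) will also be sent out", and it "will also be sent out at years 1 to year 5 post randomisation".
- The visit is counted from surgery: "Patients will be required to attend a clinic appointment for the AKSS assessment at 2 months, 1 and 5 years post operation".

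Table 1 gives a collection mode for each measure at each time point. At 5 years the OKS carries the postal symbol. AKSS, X-rays and complications carry the clinic symbol.

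Where an OKS is taken in clinic, the article says so. Table 1 marks the preoperative OKS as a clinic measure. At 1 year, if more than 12 weeks passed between randomisation and operation, "an additional OKS will be administered at the clinical assessment 1 year post surgery". Nothing comparable is given for 5 years.

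On missing data, the sample-size section says that adjustment for baseline and account of the delivery unit should add precision, and then: "Offsetting this will be any missing data which would have the reverse impact". It also says, without a figure, that 250 per arm leaves room for some non-response, on the ground that the true difference is likely to exceed 2.0. Under Statistical analysis, the principal analysis is a regression of the OKS at each time point separately. Missing data are left to secondary analyses, and a repeated-measures model is described as complementary.

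**The concern.** The primary outcome at the time point of the primary analysis depends on a returned postal form, while secondary measures are taken in person from the same patients at about the same time. On the published schedule, a patient could attend the 5-year clinic, have the AKSS recorded, and leave without being asked for an OKS form that never came back.

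Two things are at stake. The first is precision. A regression on the 5-year score alone draws no outcome information from a patient without that score, and the base-case sample size contains no numerical margin for loss. The second is bias. Patients who do not return forms may differ in outcome from those who do, and secondary analyses can only explore that under assumptions. An observed score removes the need for the assumption in that patient.

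**Working it through.** **Inputs.** From the sample-size section: 250 per group, difference 2.0, SD 8.0, two-sided 5%, stated power 80%. The article gives no rate of unreturned forms (m) and no share of them recoverable at a visit (r), so both are assumptions here: m = 10% to 20%, r = 25% to 50%.

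**The plan's own figure.** Two-sample normal approximation:

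- Required n per group = 2 × (1.960 + 0.842)² × 8.0² / 2.0² = 251.2, rounded up to 252.
- Power at 250 per group: SE = 8.0 × √(2/250) = 0.7155; 2.0/0.7155 − 1.960 = 0.835; Φ(0.835) = 79.8%.

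The stated 80% is reproduced, with every patient contributing a score.

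**With unreturned forms.** Analysed n per group = 250 × (1 − m) without clinic back-up, and 250 × (1 − m × (1 − r)) with it. Power uses the same formula.

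| Unreturned (m) | Recovered at visit (r) | Analysed per group | Power |
|---|---|---|---|
| 0% | not applicable | 250 | 79.8% |
| 10% | none | 225 | 75.5% |
| 10% | 25% | 231.25 | 76.7% |
| 10% | 50% | 237.5 | 77.8% |
| 20% | none | 200 | 70.5% |
| 20% | 25% | 212.5 | 73.1% |
| 20% | 50% | 225 | 75.5% |

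From unrounded values, the gain from clinic completion is 1.1 to 2.2 points at 10% unreturned and 2.6 to 5.0 points at 20%.

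**With baseline adjustment.** The principal analysis adjusts for the minimisation factors, which include baseline OKS. If the baseline correlation is ρ, the residual SD is 8.0 × √(1 − ρ²). The article gives no ρ; 0.3 and 0.5 are assumed.

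| ρ | Complete data | 10% missing | 20% missing |
|---|---|---|---|
| 0.3 | 83.4% | 79.4% | 74.6% |
| 0.5 | 89.8% | 86.5% | 82.3% |

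Adjustment raises the level of power. Against complete data at the same ρ, the cost of missing scores remains: 4.0 and 3.3 points at 10% missing, 8.8 and 7.5 points at 20%.

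**Timing.** The form is due 5 years after randomisation and the visit 5 years after operation. The visit therefore falls later by the wait for surgery, so an outstanding form can be identified before it. The article expects only a small number of patients to have waits long enough to distort the 1-year assessment.

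**The case against.** The strongest objection is that the article is silent on what happens to unreturned forms. A reader might infer from Table 1 that they stay missing. The documents do not support that: the table gives the planned mode of collection, and reminders, telephone contact or a replacement copy may well be in the full protocol, which an article condenses. This stands, and the point is limited to what the schedule does state, namely a postal mode with no clinic OKS at 5 years.

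A reader might also infer that the trial has no room for loss. That goes too far. The sample-size section claims qualitative room if the true difference exceeds 2.0, and for a difference of 3.0 at SD 10.0 power is still 88.9% with 10% missing. Baseline adjustment may restore most or more than all of the stated 80%, depending on the correlation.

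Postal collection also has a rationale in an unblinded trial: it keeps the patient's report away from the treating hospital and uses one mode and one clock for everyone. That argues for keeping post as the first route. It is a weaker argument against a back-up used only when no form has arrived, completed alone and before the clinician is seen. The 1-year clinic OKS was introduced to correct timing, not to recover forms, so it shows feasibility only.

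Finally, non-returners may also miss the visit, and the article links only the first two visits to routine follow-up. The recovery rate is therefore uncertain and the lower end of the gain is small. That stands too.

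**Conclusion.** This is an inexpensive improvement to data collection at the primary time point. It is not a contradiction or an error in a stated figure. The text and Table 1 agree with each other, and the power statement reproduces.

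What the document establishes is that the 5-year OKS is scheduled by post with no clinic back-up, although attendance at a 5-year visit is required and the OKS is taken in clinic elsewhere in the trial. Completion of outstanding forms at that visit would add observed primary scores that the principal analysis can use.

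The size is modest: about 1 to 5 points of unadjusted power, resting wholly on assumed rates of non-return and recovery. Effective postal chasing would shrink the gain. The reduction in non-response bias cannot be quantified from the documents, but actual scores from non-returners are something that neither covariate adjustment nor a missing-data model can provide.

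**What to change.** Change the 5-year OKS entry in Table 1 to postal, with self-completion on paper at the 5-year clinic, before the patient sees the clinician, if the form is still outstanding. Then:

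- set a time window for accepting a clinic-completed score as the 5-year value;
- record the mode and date of completion;
- include these scores in the principal 5-year analysis, and repeat that analysis without them as a sensitivity analysis.

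The change needs a short amendment and no extra visit. Its costs are that sites must check before each visit whether the form has been received, that a few scores will differ in mode, and that those scores will fall somewhat later than 5 years post randomisation. The window and the sensitivity analysis address the last two.

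Recruitment began in January 2010, so the first 5-year forms fall due in January 2015. At the article's status date of May 2013, the change could still precede all 5-year data.
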